#### Elimination Criteria

(1) Patients who do not meet the criteria for a diagnosis of ULPSS and are mistakenly included.

(2) Patients who have serious adverse events (SAEs), special physiological changes and complications, and should not continue the test.

### Sample Size

The purpose of this study was to evaluate the efficacy of FA in the treatment of ULPSS. According to previous research and clinical experience, the effective rate of TA is about 65%, and the effective rate of FA will probably reach 85% (31). The significance test level is 0.05, and the test power is 0.9. The sample size is calculated by using:

$$\begin{array}{l} N=P\left(1-P\right){\left(\frac{\alpha +\beta }{\delta }\right)}^{2} \end{array}$$

where N is the required sample size for each treatment group, and the sample size of each group is equal. When α is 0.05 and β is 0.1, the normal distribution quantile table shows that:

$$\begin{array}{l} Z_{\text{α}/2}=1:645 \end{array}$$

and

$$\begin{array}{l} Z_{\text{β}/2}=1:282 \end{array}$$

P_0_ and P_1_ represent the original curative effect and the expected curative effect, 65 and 85%, respectively. δ represents the mean difference between two groups, by substituting the above parameters and values into the formulas, 49 cases will be needed for each group. Accounting for a 10% expulsion rate, the final estimated sample size will be about 54 cases per group (108 in total).

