#### Primary Outcomes

The main result is the MAS, which is the most widely used clinical spasm scale (32). It is usually used to obtain the baseline evaluation of increased muscle tone, monitor the course of the disease, determine the effectiveness of drugs, and rehabilitation interventions, so as to reduce the overall increase of muscle tension, normalize the muscle tone of the selected muscle group, and guide physical therapy and other treatment decisions. It has the advantages of simplicity, time saving, and convenient operation. It is divided into 6 levels, i.e., 0, I, I +, II, III, and IV. Scoring methods, i.e., 0, 1, 2, 3, 4, and 5 points, represent 0, I, I +, II, III, and IV, respectively. The higher the MAS score, the more serious the spasticity. Compared with the lower limbs, the reliability of the upper limbs is better (33). The specific contents of MAS are shown in Table 3.

**Table 3 T3:** The modified Ashworth score (MAS)-specific scoring rules.

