#### Secondary Outcomes

The FMA-UE, CSS, and MBI were secondary outcome indicators.

The FMA-UE is often a widely used evaluation tool for evaluating upper extremity motor function during stroke rehabilitation. It can effectively, stably, and sensitively reflect the changes in patients' dysfunction with good reliability and validity (34, 35). Evaluate the flexion, coordination, range of motion, stability, and coordination of each joint of the patient's upper limb, which is composed of 33 items in four parts: hand, wrist, elbow, and shoulder, with a total score of 66. The lower the score, the more serious the upper extremity dysfunction. The minimum clinically important difference (MCID) of FMA-UE was 4.25–7.25 points (36). That is, if the difference in upper extremity motor function score before and after treatment is >MCID, it is considered that the upper extremity motor function of the patient has been improved, the treatment is effective and can surpass the random error (37).

The CSS was determined by the “Fourth National Conference on Cerebrovascular Diseases” (1995), which is mainly to evaluate the curative effect and is divided into basic cure (the score of functional defect was decreased by 91–100%, and the degree of disability was grade 0), significant effect (the score of functional defect was decreased by 46–90%, and the degree of disability was grade 1), improvement (the functional defect score was decreased by 18–45%), and ineffective (the functional defect score decreased by about 17%). The score is simple and easy to use (38).

The MBI is a standard scale that is widely used to evaluate the dysfunction of basic activities of daily living, which consists of 10 daily life activities, such as bathing, toilet, eating, and dressing, with a total score of 100. The higher the score, the better the self-care ability in daily life (39).

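### The sample size rests on an undefined effective rate that is not linked to the MAS, so the stated 90% power is unsupported for the primary comparison

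*Protocol article*

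**What the plan says.** Under Primary Outcomes the protocol article names one main endpoint: "The main result is the MAS, which is the most widely used clinical spasm scale". It is an ordinal score: "Scoring methods, i.e., 0, 1, 2, 3, 4, and 5 points, represent 0, I, I +, II, III, and IV, respectively". No responder cut-off is given. Table 1 schedules the MAS at allocation and at week 4.

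The Sample Size section works with two proportions: "the effective rate of TA is about 65%, and the effective rate of FA will probably reach 85" per cent, attributed to previous research and clinical experience with one citation. P0 and P1 "represent the original curative effect and the expected curative effect, 65 and 85%, respectively", while "δ represents the mean difference between two groups". It adds that "The significance test level is 0.05, and the test power is 0.9". The result is 49 per group, raised to 54 (108 in total) for a 10% loss.

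Under Secondary Outcomes, the CSS is the scale "which is mainly to evaluate the curative effect and is divided into basic cure" and three lower grades. The same section calls treatment effective when the change in FMA-UE exceeds the minimum clinically important difference. Both scales are listed as secondary.

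The Statistical Analysis section gives chi-square or Fisher tests for classified variables and a t-test or rank-sum test for continuous ones. It does not say which applies to the MAS.

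**The concern.** A power statement holds for one endpoint, one effect size and one test. Here the endpoint in the calculation is a response rate with no stated scale or cut-off, and the endpoint named as primary is a six-level score. Nothing in the article connects them. A reader who sees power of 0.9 next to a MAS primary outcome will assume that the trial has a 90% chance of detecting a worthwhile MAS difference, and no figure in the article supports that.

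What is at stake is how the result will be read. If the MAS comparison turns out non-significant, nobody can say whether the trial was large enough to detect a difference worth having, because no such difference was stated.

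**Working it through.** **1. The plan's own figure.** Inputs from the Sample Size section: rates 0.65 and 0.85, so δ = 0.20; quantiles 1.645 and 1.282. The printed formula, with the quantiles in place of α and β and P = 0.65, gives

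N = 0.65 × 0.35 × ((1.645 + 1.282)/0.20)² = 0.2275 × 214.2 = 48.7, so 49.

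The mean rate P = 0.75 with 1.96 in place of 1.645 gives 0.1875 × (3.242/0.20)² = 49.3, which also rounds to 49. For losses, 49 × 1.10 = 53.9, so 54. The stated numbers reproduce, and every input is a proportion or a normal quantile. No MAS quantity enters.

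**2. Which outcomes could carry the rate.**

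| Outcome | Status | Rule for 'effective' or 'curative effect' in the article |
|---|---|---|
| MAS | Primary | None |
| CSS | Secondary | Four grades by percentage fall in score |
| FMA-UE | Secondary | Change above the minimum clinically important difference |
| MBI | Secondary | None |

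**3. What 49 per group gives on the MAS.** Assume a two-sided 0.05 comparison of two means. By the normal approximation the detectable standardised difference is d = (z for α/2 + z for power) × √(2/n).

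- 90% power, n = 49: (1.960 + 1.2816) × √(2/49) = 0.655
- 80% power, n = 49: (1.960 + 0.8416) × √(2/49) = 0.566
- n = 54: 0.624 and 0.539

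The exact t-test at n = 49 gives 0.66 and 0.57. For a rank-sum test, dividing by √0.955 (its relative efficiency under normality) gives about 0.68 and 0.59. Ties on a six-level scale could shift these a little.

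Power at 49 per group (normal approximation) is 32% for a true difference of 0.3 SD, 70% for 0.5 SD and 93% for 0.7 SD.

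**4. In MAS points (illustration).** The article gives no SD. Over an assumed range of 0.8 to 1.2 points, 0.66 SD is 0.66 × 0.8 = 0.53 to 0.66 × 1.2 = 0.79 points. For an assumed difference of 0.5 points at 90% power, n = 2 × (3.2415 × SD/0.5)² gives 54 per group at SD 0.8, 85 at SD 1.0 and 122 at SD 1.2.

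**5. Does the 90% hold for the effective rate?** The printed formula has one P(1−P) term, whereas a difference between two groups carries the variance of both. With pooled variance under the null hypothesis and n = 49:

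z = (0.20 × √49 − 1.960 × √(2 × 0.75 × 0.25)) / √(0.65 × 0.35 + 0.85 × 0.15) = (1.400 − 1.200)/0.596 = 0.335

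Power is about 63% two-sided. One-sided, with 1.645, it is about 75%. At 54 per group the figures are 67% and 78%. For 90% power the same test needs 97 per group two-sided or 79 one-sided.

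**The case against.** The strongest defence is that the cited source may define effectiveness by a fall in MAS grade, in which case the rate would be a form of the primary outcome. That cannot be excluded from the article, so the flat statement that the trial was sized on a different outcome goes too far. What stands is that the article does not make the link. Even a MAS responder rate would be a different comparison from one of MAS scores.

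Second, the Statistical Analysis section assigns no test to the MAS, and the MAS is described as having six levels, so an analysis by category is not ruled out. The 0-to-5 scoring makes a score comparison the likelier reading, but it is an inference. That is a reason to name the test.

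Third, a full protocol or analysis plan may hold a responder definition. This would fill part of the gap. It would not turn a calculation on proportions into a power statement for a score.

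A reader might go on to infer three stronger things. One is that the trial is underpowered on the MAS: the article gives no MAS difference or SD, and a true difference of about 0.66 SD or more would be covered. Another is that the rate must be the CSS rate because both are described as a curative effect: the FMA-UE also has a rule for effective treatment. The third is that success will later be claimed on the effective rate: the article names one main result and nowhere lists the effective rate as an outcome, so this is speculation.

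**Conclusion.** The point holds in a limited form. The effective rate of 65% against 85% is neither defined nor tied to the MAS, so the stated 90% power is unsupported for the primary comparison. True power there is unknown: about 32% to 93% at 49 per group for assumed differences of 0.3 to 0.7 SD. These figures assume a two-sided 0.05 comparison of week-4 scores with 49 evaluable per group. The SD range of 0.8 to 1.2 points is an assumption used only for scale.

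Nor should a reader infer that the 90% is sound for the effective rate and merely attached to the wrong endpoint. By a standard two-group test, 49 per group gives about 63% two-sided or 75% one-sided for 65% against 85%. As written, the article supports 90% power for neither quantity.

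**What to change.** Leave the number of patients as it is and change the wording.

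1. State that the MAS at week 4 is the sole primary outcome and name the test that will compare it.
2. Replace the 90% claim with what the design delivers, for example: with 49 evaluable patients per group and a two-sided 0.05 t-test, the trial has 90% power for a standardised MAS difference of about 0.66 and 80% for about 0.57. If the rank-sum test is chosen, say that the detectable differences are slightly larger.
3. Beside this, give the target MAS difference and the SD, each with its source, so that a reader can judge whether 0.66 SD is plausible and worthwhile.
4. Define the effective rate by scale and cut-off, label it secondary, and do not present 49 per group as giving 90% power for it.

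The cost is a protocol text change, best made before outcome data are analysed. If the sourced MAS target proves smaller than the design can detect with 90% power, the text should say so and report the power actually available.

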### Randomization

Eligible patients were allocated, in a 1:1 ratio were randomly assigned to the experimental group or the control group, following the randomization principle, which employs block randomization to generate random-number sequence using the SPSS, and an independent statistician who did not participate in the treatment and result evaluation was responsible for processing the results. Meanwhile, we also prepared sealed opaque envelopes with group information strips in these envelopes, which was hidden until the informed consent was obtained.

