### Statistical Analysis

After all the experimental data are verified to be correct, SPSS19.0 statistical software is used for statistical analysis. Classified variables will be analyzed using Pearson's χ^2^ test or Fisher's exact test, and continuous variables will be evaluated using Student's *t*-test or an appropriate non-parametric method. The statistical results are measured by the mean ± standard deviation (SD; *x* ± s); when comparing within or between groups, tests for normality and homogeneity of variance are performed prior to data analysis for each group. If the data satisfy normal distribution and homogeneity of variance, the *t*-test will be used for comparisons between two groups, and the least significant different (LSD) or Student-Newman-Keuls (SNK) method will be used for multiple comparisons. Instead, the rank-sum test will be used for non-normality or non-uniformity of variance. Set the test level as 0.05, *p* < 0.05, and the difference was statistically significant.

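### The sample size comes from a one-sample formula: 49 per group gives about 63-65% power (two-sided 0.05) for 65% versus 85%, not 90%

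*Protocol article*

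**What the plan says.** All of the following is in the protocol article.

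- **Sample Size, assumptions:** "the effective rate of TA is about 65%, and the effective rate of FA will probably reach 85" per cent. For the error rates: "The significance test level is 0.05, and the test power is 0.9".
- **Sample Size, formula:** N equals P(1-P) times the square of (α + β)/δ, where α and β stand for their normal quantiles. N is defined for each arm: "where N is the required sample size for each treatment group, and the sample size of each group is equal". δ is described as the difference between the two groups. The quantiles are given as 1.645, labelled with α/2, and 1.282, labelled with β/2. The section does not say which value was used for P.
- **Sample Size, result:** "by substituting the above parameters and values into the formulas, 49 cases will be needed for each group". Then: "Accounting for a 10% expulsion rate, the final estimated sample size will be about 54 cases per group (108 in total").
- **Randomization:** "Eligible patients were allocated, in a 1:1 ratio".
- **Statistical Analysis:** "Classified variables will be analyzed using Pearson's χ^2^ test or Fisher's exact test", at level 0.05, with no mention of one-sided testing.

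**The concern.** A formula with one P(1-P) term gives the size of a single sample tested against a known, fixed rate. Here both rates are estimated, one in each randomised arm, so the variance of the difference is the sum of two binomial variances. Leaving one out roughly halves the required number per group.

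The quantile is a second problem. With α = 0.05, the value that belongs to α/2 is 1.96. The printed 1.645 corresponds to a one-sided 5% test, or a two-sided 10% test, and the Statistical Analysis section announces neither.

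This calculation is the only justification given for 108 patients and the only power claim in the document. If it is wrong, a non-significant comparison of effective rates would be presented as coming from a trial with a 10% chance of missing a 20-point difference, when the real chance is more than one in three (two-sided) or about one in four (one-sided).

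**Working it through.** **Inputs (Sample Size section):** P0 = 0.65, P1 = 0.85, δ = 0.20, quantiles 1.645 (as printed) and 1.282 (90% power). The two-sided 0.05 quantile is 1.96. The mean rate is 0.75. The single-group variances are 0.65 × 0.35 = 0.2275 and 0.85 × 0.15 = 0.1275, with sum 0.355. Twice the variance at the mean rate is 2 × 0.75 × 0.25 = 0.375.

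**1. Reproducing 49.** With one variance term:

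- P = 0.65 and 1.645: 0.2275 × (2.927/0.20)² = 48.7, which rounds up to 49.
- P = 0.75 and 1.96: 0.1875 × (3.242/0.20)² = 49.3, about 49.
- P = 0.75 and 1.645: 0.1875 × (2.927/0.20)² = 40.2, which does not match.

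The first route uses the quantiles as printed. Both matching routes are one-sample calculations, so the missing term is not a slip in typesetting the formula: the answer was computed without it.

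**2. Size needed for two groups at 90% power.**

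| Formula, per group | Two-sided 0.05 (1.96) | One-sided 0.05 (1.645) |
|---|---|---|
| Unpooled: 0.355 × ((z_α + 1.282)/0.20)² | 93.3 → 94 | 76.0 → 77 |
| Pooled: ((z_α√0.375 + 1.282√0.355)/0.20)² | 96.4 → 97 | 78.4 → 79 |
| Mean rate: 0.375 × ((z_α + 1.282)/0.20)² | 98.5 → 99 | 80.3 → 81 |

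With a continuity correction the pooled figures rise to 107 and 89. None is near 49.

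**3. Power at 49 per group.** Standard error of the difference: √(0.355/49) = 0.0851 (unpooled), √(0.375/49) = 0.0875 (under the null).

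- Two-sided, unpooled: 0.20/0.0851 - 1.96 = 0.39, power 65.2%.
- Two-sided, pooled: (0.20 - 1.96 × 0.0875)/0.0851 = 0.335, power 63.1%.
- One-sided, the same two forms with 1.645: 76.0% and 74.5%.
- Exact binomial enumeration: Pearson chi-square 64.0% two-sided and 75.3% one-sided; Fisher's exact test 55.5% two-sided.

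**4. Power if all 54 per group are evaluable.** Two-sided 67.4% (pooled) to 69.4% (unpooled), exact chi-square 68.2%, Fisher 59.9%. One-sided 78.1% to 79.4%.

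**5. Effect detectable with 90% power at 49 per group, two-sided.** For 65% versus 91% the power is 88.6% (pooled), 90.5% (unpooled) and 90.3% (exact chi-square). The detectable gap is therefore about 26 points, not 20.

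**The case against.** The strongest reply accepts the formula error but disputes how the loss is presented.

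- **Sidedness.** The formula error alone, keeping the printed 1.645, brings power down to about 75-76%. The further drop to 63-65% depends on reading 0.05 as two-sided, which the document never says outright. This is fair, and both figures are given here. The two-sided reading is still the better supported: the quantile carries an α/2 label, and the analysis is a chi-square or Fisher test at 0.05 with no one-sided qualification.
- **The 1.645 may be only a misprint.** If P = 0.75 and 1.96 were actually used, the printed quantile is a labelling slip. That is possible, but this route is also single-variance and gives the same 49, so the power is unaffected.
- **The primary outcome is the MAS score.** The power figures concern a responder comparison, and no effective rate is defined on the MAS. This stands as a limit: the results apply to 65% versus 85% only, and power for the MAS comparison cannot be worked out from the document. It does not rescue the claim of 90%, which is made for those two rates.
- **Enlarging the trial is also possible.** True, since the Trial Status section says recruitment was continuing. That choice is the sponsor's; correcting the stated figure does not depend on it.

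The allowance for a condensed article does not help. The formula, inputs and answer are all printed, and no further detail could make 49 per group yield 90% for these rates.

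**Conclusion.** The concern holds and must be fixed. For effective rates of 65% and 85%, 49 evaluable patients per group give about 63-65% power with a two-sided test at 0.05 (chi-square or its normal approximation; about 56% with Fisher's exact test) and 75-76% with a one-sided test. Even the most generous case, one-sided with no losses from 54 per group, stays below 80%. The conclusion rests on the document's own rates, level and 1:1 allocation; only the choice between the two ranges depends on sidedness.

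**What to change.** In the Sample Size section:

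1. Replace the formula with a two-sample one, for example N = [P0(1-P0) + P1(1-P1)] × ((z for α/2 + z for β)/δ)², or the pooled version, and name the version used.
2. State that the test is two-sided at 0.05, with 1.96 for α/2, and label 1.282 as the quantile for β rather than β/2.
3. Restate the power at the fixed size: about 63-65% with 49 evaluable per group, or 67-69% with 54, for 65% versus 85%. Equivalently, say that 90% power is available only for about 65% versus 91%. If Fisher's exact test is to be the main test, give its lower figure (56% at 49 per group).

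This is a wording change. It needs no extra patients and leaves the trial's conduct as it is; the cost is a less favourable stated power. If the sponsor prefers to keep 90% power for a 20-point difference, about 97 evaluable patients per group are needed, which with 10% losses is 97/0.9 = 107.8, or 108 per group (216 in total).

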### Recruitment

We had formulated plans and methods related to subjects, such as preparing informed consent, and obtaining necessary data, videos, and pictures to help subjects to understand the purpose and procedure of the trial. We had also explained the advantages and disadvantages of this treatment and relevant safety measures to be taken during the trial.

In addition, we had put up recruitment posters in hospitals and community billboards and used the Internet for publicity and recruitment. The research group had conducted preliminary judgment and screening on each participant according to the above inclusion and exclusion criteria, conducted a final review after signing the informed consent, and those who passed the review were included in the test.

### Interventions

The experiment was divided into two groups: the experimental group and the control group. The two groups of patients received different treatments five times a week for 4 weeks. At the same time, each patient received symptomatic treatment and supportive treatment. On the basis of routine rehabilitation treatment, acupuncture was used in the groups. The experimental group was treated with FA, and the control group was treated with TA.

#### Experimental Group

Acupoints used were Daling (PC7), Hegu (LI4), functional acupoint 1, and functional acupoint 2. The locations are specifically presented in Table 2. Operation: Sterile acupuncture needles (single tube needles) of 0.30 mm × 75 mm, 0.30 mm × 30 mm were used (produced by Wuxi Jiajian Medical Instruments Co., Ltd.). Routine disinfection of the acupuncture site, Step 1, quick puncture PC7: we used 30 mm × 30 mm one-time filigree needle to quickly pierce in the direction of the palm and heel. After “Deqi,” repeatedly lifted and twisted the needle. The twisting frequency was 100 times/min, and the lifting time was 30 s. There was no need to leave a needle after obtaining a strong needle sensation in the local tissue (touching the inductance to the fingertip). Step 2, 0.30 × 75 mm filiform needle was punctured 50~60 mm from LI4 to SI3 direction. After “Deqi,” it was repeatedly lifted, inserted, and twisted. The twisting frequency was 60 times/min and the lifting and inserting time was 1 min. The needle was retained after the strong needle feeling of deep tissue was obtained and the finger spasm was relieved immediately. Step 3: Electrical stimulation of functional points: we used g6805-a electroacupuncture instrument at functional point 1 and functional point 2, density wave; Negative pole was connected to functional point 1 and positive pole was connected to functional point 2. The pulse current was stopped when the patient had slight muscle contraction. We gently adjusted the direction and depth of the needle tip of functional point 1, so that the five fingers of the affected hand was extended at the same time and the back of the wrist was extended. We kept the needle for 30 min. The treatment was performed once a day, 5 times a week for 4 weeks. The curative effects were evaluated before and after treatment.

**Table 2 T2:** Location of acupoints for treating post-stroke upper limb spasticity.

